### Statistical analysis plan

Data analysis, using the following analysis plan, will be blind to the allocation arm.

#### Descriptive analysis

For each treatment arm we will describe the participant age (mean and standard deviation), birth weight, gender of baby, number of previous children, the eligibility qualifying criteria, and socioeconomic factors.

#### Recruitment and retention

Recruitment rate will be calculated as the proportion of women invited to take part compared with the number of women: responding to the invitation; meeting the eligibility criteria; and recruited into the trial.

The retention rate will be calculated as the proportion of women starting the study to those completing to 24 weeks post recruitment.

#### Mediterranean diet score

Analysis of covariance, adjusting for baseline MD score and using a significance level of 5%, will be used to compare the mean change in MD score from baseline to 12 and 24 weeks between the two groups. As this is a pilot study with a small sample size we will only be able to explore any indications of sustained adherence to the MD.

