### Trial design

We are carrying out a two-arm, pilot, parallel-group RCT. Trial participants are being recruited from two maternity service sites in Scotland, both with dating scan appointment rates of approximately 100 per month. Eligible participants receive either: diet advice and support, with a supporting MD resource booklet, in addition to standard care; or standard care with no additional dietary advice/support/materials.

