### Recruitment

#### Hospital/community treatment centre

We have recruited one hospital and one community treatment centre in the same NHS Scotland Board/region that carry out dating scans.

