### Randomisation

Participating women are randomised when visiting the hospital for their dating ultrasound scan. Allocation to the intervention arm or control arm is by restricted randomisation (by site), via pre-randomised sealed envelopes, based on a predetermined random number allocation. This randomisation has been carried out by an independent statistician. Participants are randomised after consent has been obtained and immediately after the first MD questionnaire has been completed. Participants are enrolled for a total of ~6 months (that is, from 12 to 36 weeks of pregnancy).

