#### Measurement of potential confounders

We are collecting data related to potential confounders such as the baby’s birth weight, sex, socioeconomic status, maternal education level and exposure to smoking during pregnancy. Given the small sample size in this pilot trial, there will be a limit to how many confounders it will be possible to adjust for in the analysis; however, we will be able to describe their distribution in the two groups.

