### Sample size

Our intention is to continue recruitment until we have 50 women included in the trial in order to answer our research questions. Both centres have approximately 100 dating scans per month, but there is seasonal variation. We estimate that at least 800 invitations will be made, and those who do not respond prior to the ultrasound scan appointment have a further opportunity to take part if they respond to the clinic poster. Of the 800+ invitations made, we estimate that one-quarter (*n* = 200) will fulfil the eligibility criteria (‘Do you (the mother), or the father, or sibling of the baby have an allergic disease …?’). This estimate is based on an overall assessment of the epidemiology of allergic disorders in Scotland, systematic reviews of a number of previous primary prevention trials [26,27] and a recent dietary intervention trial in pregnant women [14]. Based on our discussions with consumer representatives that have informed this pilot trial, we anticipate that ~25% (that is, *n* = 50) of eligible women will be willing to take part and, with an estimated 20% attrition/incomplete data collection during the course of the pregnancy, we anticipate that 40 participants will complete the study. If these assumptions are fulfilled, recruitment and retention will be comparable with other leading international primary prevention trials [27].

As this is a pilot trial, using a questionnaire based on Castro-Rodriguez and colleagues [18], we estimate that using a level of 0.05 (two-tailed) and power of 80% will require a sample size of 40 to detect a statistically significant difference in the mean MD score of the intervention group, from baseline, in the order of 3 units.

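### Randomisation is restricted by site, but the stated ANCOVA for MD score has no site term; if the sites differ after baseline adjustment, its standard error is too large

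*Protocol article*

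**What the plan says.** **Design.** The Trial design section states that "Trial participants are being recruited from two maternity service sites in Scotland". The Recruitment section describes them: "We have recruited one hospital and one community treatment centre in the same NHS Scotland Board/region". Under Randomisation: "Allocation to the intervention arm or control arm is by restricted randomisation (by site), via pre-randomised sealed envelopes". The type of restriction, the block size and the expected split of participants between sites are not given.

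**Analysis.** Under Statistical analysis plan, subsection Mediterranean diet score, the method is "Analysis of covariance, adjusting for baseline MD score and using a significance level of 5" per cent, used to "compare the mean change in MD score from baseline to 12 and 24 weeks between the two groups". Baseline MD score is the only covariate named.

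**Other covariates.** The section on potential confounders says that "there will be a limit to how many confounders it will be possible to adjust for in the analysis". Its examples are birth weight, sex, socioeconomic status, maternal education and smoking exposure. Site is not among them, and no further model term is fixed.

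**The concern.** When arms are balanced within a factor, differences between levels of that factor cancel from the comparison of arms. If the factor is then left out of the model, those differences still count as unexplained variation. The model reports a standard error larger than the true sampling variability of the estimate, so confidence intervals are wider than they need be and a nominal 5% test rejects less than 5% of the time under the null.

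What is at stake is precision in a small trial. The article planned 40 completers. Its Trial status section reports 30 women recruited, which would leave 30 × 0.8 = 24 completers if the assumed 20% attrition applies.

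**Working it through.** **1. The plan's own figure.** The Sample size section says that "using a level of 0.05 (two-tailed) and power of 80% will require a sample size of 40", for a difference of about 3 units. No SD is stated, so the 40 can be neither reproduced nor refuted. Solving for the SD it implies, with (1.960 + 0.842)² = 7.849:

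- two groups of 20: SD = √(20 × 3² / (2 × 7.849)) = 3.39
- paired test, n = 20: SD = 3 × √(20 / 7.849) = 4.79
- paired test, n = 40: SD = 3 × √(40 / 7.849) = 6.77

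The point does not depend on which was meant. The simulation below assumes 3.387 and a baseline–outcome correlation of 0.5, which gives a residual SD of 3.387 × √(1 − 0.25) = 2.93 units.

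**2. Formula.** Let d be the site gap in follow-up MD score that remains after baseline adjustment, in residual SDs, and p the share of participants at one site. Without a site term the residual variance is multiplied by 1 + p(1 − p)d². With arms balanced within site, the true variance of the treatment contrast is unchanged. The standard error is therefore inflated by √(1 + p(1 − p)d²), which for two equal sites is √(1 + d²/4). The large-sample type I error is 2 × [1 − Φ(1.96 × inflation)].

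**3. Results for two equal sites.** The simulation used arms balanced within site, 4,000 replicates per scenario and a true effect of 3 units for power.

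| d | SE inflation, formula | SE without / with site, simulated, N = 40 | Type I error without site: formula; simulated, N = 40 | Power without / with site, N = 40 | Power without / with site, N = 24 |
|---|---|---|---|---|---|
| 0 | 1.00 | 1.00 | 5.0%; 5.3% | 87.2 / 86.8% | 64.6 / 64.6% |
| 0.25 | 1.01 | 1.01 | 4.8%; 4.8% | 87.9 / 88.0% | 64.6 / 65.1% |
| 0.5 | 1.03 | 1.03 | 4.3%; 3.7% | 85.7 / 87.3% | 62.6 / 64.9% |
| 1 | 1.12 | 1.12 | 2.8%; 2.9% | 81.2 / 87.2% | 55.1 / 63.9% |
| 1.5 | 1.25 | 1.26 | 1.4%; 1.5% | 72.8 / 87.2% | 44.7 / 65.3% |

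With site in the model, simulated type I error at N = 40 was 4.5% to 5.2%. Simulation error on a rejection rate near 5% is about √(0.05 × 0.95 / 4000) = 0.3 points. At d = 0.5 the formula's 4.3% is the safer figure.

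**4. Second simulation.** With a true effect of 0.8 SD (smaller than 3 / 3.387 = 0.89 SD) and d = 1, power without and with site was 72% and 79% at N = 40, and 46% and 56% at N = 24. Over both simulations the loss at d = 1 is 6 to 10 points. At d = 0.5 it is about 2 points.

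**5. Where the effect shrinks or vanishes.**

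- *Gap carried by baseline.* With sites 1 SD apart at baseline and no residual gap, the ratio of the SE without site to the SE with site was 0.997 at N = 40 and 0.993 at N = 24: no inflation.
- *Unequal sites.* With p = 0.2, √(1 + 0.16 × 0.5²) = 1.02 and √(1 + 0.16 × 1²) = 1.08, against 1.03 and 1.12 for equal sites.

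**6. Scale of the gaps.** On the assumed SD, d = 0.5 is 0.5 × 2.93 = 1.5 units and d = 1 is 2.9 units. The latter nearly equals the 3-unit target effect on a scale of 22.

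**The case against.** **The article is a condensed account.** Its ANCOVA sentence excludes nothing, and a fuller plan may list site. That possibility stands; if the full plan has the term, only the article's sentence is incomplete. But the article has its own statistical analysis plan section, which names the method, the covariate and the significance level. Followed as written, it omits the one factor on which randomisation was restricted.

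**The harm is conditional and probably small.** This stands. Nothing in the article suggests that two centres in one health region differ by a full residual SD after baseline adjustment. At 0.5 SD or less the inflation is 3% or less.

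**Exact balance within site is an idealisation.** This also stands. The form of restriction is not described, and attrition can disturb balance among completers. To the extent that balance fails, the model without site is less conservative, but its estimate carries chance site imbalance, which a site term would remove.

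**Stronger readings that a reader might infer, and that the article does not support:**

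- *The standard error is too large whenever the sites differ.* Only a gap left after baseline adjustment matters, and the stated model already adjusts for baseline.
- *The treatment estimate is biased or false positives are more likely.* The error runs towards conservatism.
- *The same ANCOVA is needed for the FFQ and biomarkers.* The FFQ section plans a comparison of arms without naming a model. The biomarker section relates changes in the markers to changes in MD score.
- *The main trial would be mis-sized.* The Discussion says the pilot is to help determine sample size, but not that the MD-score residual variance will be the input.

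**Conclusion.** The point holds in conditional form. The stated model leaves out the randomisation factor. If the sites differ in MD-score outcome given baseline, and the arms are near balance within site, the standard error is overstated and the 5% test is conservative. The size cannot be fixed from the article and rests on assumed values of the residual gap, the site split and the balance achieved; the 1 SD figures are an upper illustration and not an expectation.

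Severity is low. The article's primary aims are recruitment, retention and acceptability, and MD-score change is secondary. What justifies raising the point is that the correction costs almost nothing.

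**What to change.** In the Mediterranean diet score subsection, state that the ANCOVA at 12 and at 24 weeks contains arm, baseline MD score and site (two levels). If a between-arm model is fitted for FFQ nutrient intakes or urinary biomarkers, include site there too; no such model need be added on this account.

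Site is already known for every participant because allocation was made by site, so no new data are needed. The term uses one degree of freedom. With no residual site gap, simulated power with and without site was 64.6% and 64.6% at 24 completers, and 86.8% and 87.2% at 40, so the cost is negligible. It would also help to state the type of restriction, the block size and the number recruited per site.

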### Qualitative data analysis

Recorded, end-of-trial telephone interviews with a sample of participants will be transcribed verbatim and analysed for key emerging themes, using a thematic content analysis [28].

## Discussion

The development of this trial has followed the UK Medical Research Council’s framework for developing and evaluating complex interventions [29]. In the development phase, knowledge was used to formulate theory that informed a systematic review and meta-analysis [12]. The potential intervention was therefore modelled (that is, its process and outcomes). In the current stage – that is, feasibility and piloting – this exploratory trial has been developed to refine the practicality of the intervention (for example, to test procedures, to estimate recruitment and retention, to determine sample size). This may then lead to further piloting and feasibility work, or to a large-scale RCT.

This is an innovative pilot RCT to assess rates of recruitment and retention, and adherence to a MD pattern in the second and third trimesters of pregnancy. No RCT has yet investigated the role of the MD on allergy. To test the overarching hypothesis that a MD during pregnancy will reduce the risk of allergy in newborns, testable only in a larger RCT with follow-up of the infants born, a pilot trial of this nature is an essential stepping stone; given that the available epidemiological evidence supports a link between a MD and the prevention of allergy, the trial in which we are engaged is the next step in investigating a dietary intervention. Such an intervention has the potential to offer a brief, effective and cost-effective intervention at a key stage in the lifespan, which may reduce the allergy burden on individuals and on the NHS.

### Reporting and dissemination

Reporting will adhere to CONSORT [30]. A final report will be submitted to the funding body (Chief Scientist Office). Papers will be prepared for publication in peer-reviewed journals. Articles reporting the results will be circulated to all collaborators.

### Trial governance

In accordance with Good Clinical Practice Guidelines [31] and NHS research governance requirements, a Project Management Committee has been formed, which commented on proposed changes to the protocol and is monitoring the trial. An independent academic is overseeing any trial steering and data-monitoring and ethics matters that may arise.

### Trial timeline

The trial started 1 May 2012. Invitations/recruitment material sent to potential participants (pregnant women telephoning a centralised booking system to arrange a dating scan appointment). Participants randomised to the intervention arm or control arm at dating scan appointments was ongoing from June to December 2012. Start of 12-week follow-up is ongoing from September 2012. Start of 24 week follow-up is ongoing from December 2012. Planned trial end date is end July 2013. Duration of trial is 15 months.

## Trial status

At the time of submission, 22 participants had been recruited. At the end of recruitment (December 2012), 30 participants had been recruited.

## Abbreviations

FFQ: Food frequency questionnaire; MD: Mediterranean diet; NHS: National Health Service; RCT: Randomised controlled trial
